#### Power calculation

The sample size calculation is based on a minimal clinically important difference (MCID) of 3.4 [62] and pooled standard deviation (SD) of 6.0 for the change in POEM score [52]. With 80% power, and 5% two-sided alpha, each treatment group would require 50 participants. Allowing for 15% withdrawal and loss to follow up, 118 participants total are required for this study.

#### Participant safety

A study specific safety plan is in place for the trial. AEs will be identified by participant diaries, at pharmacy visits, or by ad-hoc contact from participants to the study team. Participants are prompted in their weekly diary with an open question asking if they have experienced any changes in their health or if they have experienced worsening eczema in the last week in order to capture all a wide-variety of adverse events. Any affirmative response results in contact from central MRINZ investigator for formal AE collection. All AEs are reviewed by the study doctor and coordinating team within 24 hours. An Independent Data and Safety Monitoring Committee (DSMC) is appointed to monitor all adverse events on a three-monthly basis, and will be informed of any SAEs within 72 hours. If safety concerns are expressed by the DSMC, unblinded study data may be made available to them on request. The DSMC may advise the study should be halted or terminated in the case of significant concerns for the safety of participants. AEs will be reported every six months to Medsafe, the New Zealand Medicine and Medical Devices Safety Authority. Indemnity insurance is in place for study sponsor for claims resulting from trial participation.

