### Participant timeline

Upon presentation to the pharmacy, consent, demographic data, eligibility, and baseline data are collected, followed by a clinical photograph of a representative eczema lesion, chosen by the participant. The participant is randomised, and the appropriate treatment is dispensed by the study pharmacist along with the aqueous cream. Over the six-week interventional period, participants complete a weekly digital diary to report POEM, treatment adherence, adverse events, and use of concomitant medications (Table 2). Participants return to the pharmacy for a second face to face visit at week six including a second clinical photograph of the representative lesion. A final electronic follow up survey is completed at week eight to collect any adverse events following the cessation of study treatment. The study flow is depicted in Fig. 1*.*

**Table 2 Tab2:** Summary of study procedures

	Visit 1	Treatment Period					Visit 2	Follow Up Survey
Day	**0**	**7**	**14**	**21**	**28**	**35**	**42 (+ 5)**	**14 days post Visit 2 (+ 5)**
Eligibility screen	X							
Informed consent	X							
Demographic data collection	X							
POEM	X	X	X	X	X	X	X	
PO-SCORAD	X						X	
SCORAD (Part B)	X						X	
DLQI	X						X	
Eczema photo	X						X	
Randomisation	X							
Dispense medication	X							
Electronic study diary		X	X	X	X	X		
Treatment compliance		X	X	X	X	X	X	
Adverse event collection		X	X	X	X	X	X	X
TSQM Version II							X	
Acceptability NRS							X

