### Retention

Participants are reimbursed $200 (NZD) in recognition of travel and time. Reminders for weekly study diary completion are sent to non-responders once daily for five days, after which the diary window is closed.

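### A missed weekly diary leaves seven treatment days that no later diary asks about; adverse events have a late backstop at Visit 2, but medication and escalation data have none stated

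*Protocol article*

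**What the plan says.** - **The safety question.** Under Participant safety, the weekly diary prompts participants with an open question "asking if they have experienced any changes in their health or if they have experienced worsening eczema in the last week". What follows a yes is stated: "Any affirmative response results in contact from central MRINZ investigator for formal AE collection".
- **The medication question.** Under Permitted and prohibited concomitant treatment, the diary asks about use of medication other than the study treatment, again over the preceding week. The central team then contacts the participant to complete the medication form.
- **Closure.** Under Retention: "Reminders for weekly study diary completion are sent to non-responders once daily for five days, after which the diary window is closed".
- **Schedule.** Under Participant timeline, "participants complete a weekly digital diary to report POEM, treatment adherence, adverse events, and use of concomitant medications". Table 2 marks the electronic diary on days 7, 14, 21, 28 and 35. Its row for "Adverse event collection" has those five days, Visit 2 (day 42, up to 5 days later) and the follow-up survey. Table 2 has no row for concomitant medication.
- **Other routes for adverse events.** Under Participant safety: "AEs will be identified by participant diaries, at pharmacy visits, or by ad-hoc contact from participants to the study team".
- **The week-eight survey.** "A final electronic follow up survey is completed at week eight to collect any adverse events following the cessation of study treatment". It is aimed at events after treatment, so it does not stand in for a missed treatment week.
- **Use of the data.** The secondary outcomes include the proportions of cutaneous and systemic events and of treatment escalation, compared between groups.

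**The concern.** The look-back is fixed at one week, but the interval since the participant last answered is not. When a diary closes unanswered, that interval is two weeks or more, while the next diary still asks about one. What happened in the skipped week is then outside every later diary.

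Two kinds of data are at stake, and they are protected differently. Adverse events are also collected at Visit 2 and by ad hoc report. Medication use, which is where topical corticosteroid use during a flare would appear, is described as collected in the diaries. The protocol permits habitual topical corticosteroid for up to seven days without withdrawal, so a whole permitted course can fall inside one skipped week. That bears directly on the comparison of treatment escalation between groups.

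**Working it through.** The article gives no figure for diary coverage or completion, so there is no stated figure to reproduce. The check is a day count on the stated rules.

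**Inputs.** Diaries are due on days 7, 14, 21, 28 and 35 (Table 2). The look-back is 7 days (Participant safety; concomitant treatment section). A diary can be completed 0 to 5 days late (Retention). Visit 2 is on day 42 to 47 (Table 2). Treatment lasts 42 days.

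**1. All diaries on time.** A diary completed on day c covers days c − 6 to c. The five diaries cover days 1 to 35 with no gap.

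**2. One missed diary, the others on time.** If the diary due on day d is missed, the previous one reaches day d − 7 and the next starts at day d + 1. Uncovered: days d − 6 to d, which is 7 days. For d = 14, days 8 to 14 are uncovered. Share of treatment: 7 / 42 = 16.7%. If the question refers to each diary's own week, the same 7 days are uncovered however late the neighbouring diaries are.

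**3. One late diary.** This step assumes that the look-back runs from the day of completion. A diary due on day d and completed L days late covers days d + L − 6 to d + L. If the previous diary was on time, or the late one is the first, days d − 6 to d + L − 7 are uncovered, which is L days (1 to 5).
- Day-7 diary completed on day 12: days 1 to 5 are uncovered.
- Day-14 diary completed on day 19: days 8 to 12 are uncovered.
- All five diaries 5 days late: only days 1 to 5 are uncovered in total, so the gap does not add up diary by diary.
- Question tied to the diary's own week: no gap.

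**4. Recall needed at Visit 2 for adverse events.**
- Missed day-7 diary, Visit 2 on day 42: 42 − 7 = 35 to 42 − 1 = 41 days, about five to six weeks.
- Same diary, Visit 2 on day 47: 40 to 46 days.
- Missed day-35 diary, Visit 2 on day 42: 7 to 13 days.

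**5. Who may lack Visit 2.** The power calculation allows for 15% withdrawal and loss: 0.15 × 118 = 17.7, about 18 participants. The article does not say how many of these would still be seen or telephoned.

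**6. Medication and escalation.** The concomitant treatment section names the weekly diary as the source of medication data and says that escalation will be recorded, without saying at which other contact. Steps 2 and 3 apply to the medication question, and nothing corresponding to step 4 is stated.

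**The case against.** **The article condenses fuller documents.** It refers to a study-specific safety plan and a monitoring plan, neither shown. What staff do when a diary closes unanswered could well be there. This stands. A reader might infer that a non-responder is never contacted, but the article is silent on that, and silence is not a rule. What it does state is the look-back and the closing rule, and the point rests on those.

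**The diary question is reported, not reproduced.** The time limit could attach only to worsening eczema, leaving health changes unlimited. That is possible, though the natural reading covers both. On the narrower reading the gap remains for worsening eczema and for medication, where the time limit is not ambiguous. Data capture says that each diary link belongs to a time point, so the question may refer to the diary's own week. That would remove the late-diary gap but not the missed-diary gap.

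**Visit 2 is a backstop.** It collects adverse events with no stated recall limit, and the eligibility criteria allow it by telephone if needed. This stands. A reader might infer that events in a skipped week are lost, or that the comparison of events is under-counted or biased between arms. The documents do not support either: a participant who completes Visit 2 can still report the event, and nothing shows that diary response differs by arm.

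**A loss can be put in figures only by assumption.** Supposing 10% to 20% of 118 × 5 = 590 diaries missed gives 59 to 118 of 118 × 6 = 708 participant-weeks (8% to 17%). The miss rate has no source in the document, and the result counts weeks without a diary question, not lost events. It should not be used as an estimate.

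**The Discussion does not claim complete coverage.** It says that weekly follow-up lets the team maintain safety oversight throughout participation. The diary rule does not make that statement false.

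**Conclusion.** The point holds in a limited form. On the stated rules, each missed diary leaves seven treatment days (17% of the treatment period) that no later diary asks about, given that the neighbouring diaries are on time or that the question refers to the diary's own week. A late diary leaves 1 to 5 days, but only if the look-back runs from completion and the previous diary was on time or the late one is the first.

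For adverse events the consequence is mainly delay and weaker recall, with a real hole only where there is neither a Visit 2 nor an ad hoc report. For concomitant medication and treatment escalation the article states no second source, so this is where the fixed look-back matters most. The number of events or courses missed cannot be estimated without a diary completion rate. The primary POEM analysis and the sample size are unaffected, and the documents do not contradict themselves. This is a worthwhile, inexpensive improvement to a stated method.

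**What to change.** Change the recall of the adverse-event and medication questions in the diary to: since your last completed diary, or since Visit 1 if none. Ask both questions at Visit 2 with the same recall, and show the medication question in Table 2. This also covers the final treatment week, for which Table 2 marks no diary. Leave POEM at its seven-day recall, which belongs to the instrument.

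Contact after a closed diary may already be in the safety plan and is not part of this change.

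**Cost.** A wording change to the REDCap diary and the Visit 2 form. Participants who missed a diary face a longer recall period, and so less exact dates, but the present diary would not ask them about that week at all. Recruitment began in January 2022, so the wording would change partway through; record the date of the change so that events and medication collected under each wording can be told apart. Randomisation is 1:1 in blocks of four within site, so a change on one date should fall about equally on both arms.

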## Discussion

There is increasing demand worldwide for effective botanical therapies for eczema as an adjunct to conventional treatment. This community-based randomised controlled trial will determine if in vitro evidence for mānuka oil based ECMT-154 translates to clinical benefit.

This decentralised study will use direct electronic data capture, allowing real-time remote monitoring of study visits. Weekly follow up of participants through electronic diaries allows the study team to maintain safety oversight throughout participation in the study.

Community pharmacies are well positioned to facilitate trial participation for individuals with that may otherwise be faced with barriers accessing clinical trials [63, 64]. It is anticipated this study design will provide a more generalisable result than if recruitment was conducted at a single study site, which could otherwise introduce bias on ethnicity or socioeconomic status.

A secondary outcome of this study will assess pharmacist capability for SCORAD scoring, a tool typically used by trained dermatologists. Training will be provided to pharmacists and SCORAD scores will be compared to remote dermatologist assessment. Results may help inform appropriate selection of outcome assessments for future research conducted in community pharmacies.

In conclusion, this trial will provide high quality safety and efficacy data on mānuka oil based ECMT-154 for the topical treatment of eczema. If efficacy is demonstrated, this novel topical treatment may provide a steroid-sparing emollient option for individuals with eczema.

### Trial status

At the time of submission, participant recruitment began in January 2022. Enrolment is anticipated to continue through to mid-2023. Current protocol version 2.1 dated 18th May 2022.

## Data Availability

Study results will be submitted for publication to an appropriate academic peer-reviewed journal, and will be presented at relevant conferences. Results will be shared with participant and all recruiting pharmacy sites. Findings will be reported in accordance with the CONSORT (Consolidated Standards of Reporting Trials) statement.

## Abbreviations

AE: Adverse Event
DLQI: Dermatology Life Quality Index
DSMC: Data and Safety Monitoring Committee
HDEC: Health and Disability Ethics Committee
ITT: Intention-to-treat
MCID: Minimal Clinically Important Difference
NRS: Numerical Rating Scale
PO-SCORAD: Patient-Oriented SCORing Atopic Dermatitis
POEM: Patient-Oriented Eczema Measure
PPS: Per Protocol Set
RCT: Randomised Controlled Trial
SAE: Serious Adverse Event
SCORAD: SCORing Atopic Dermatitis
SCOTT: Standing Committee on Therapeutic Trials
TSQM: Treatment Satisfaction Questionnaire for Medication
